### Intervention

#### Intervention group

Participants in the SUD experimental group will be administered the VIPP-SD, an evidence-based intervention that adopts the technique of video-feedback for enhancing (1) sensitive parenting and positive parent-child relationships and (2) sensitive discipline, reducing children’s emotional and behavioral problems [21]. The protocol is based on attachment theory [17, 47] and on social learning theory [48, 49]. The intervention is manualized and delivered in 6 sessions, each one affording themes relevant for sensitive parenting and sensitive discipline. The manual describes the structure, the themes, and the exercises suggested to parents during the different sessions [21]. Each home visiting begins with the videotaping of structured parent-child interactions, which are then reviewed together with the intervener during the following sessions. Between sessions, the intervener prepares comments for each video fragment to-be-seen according to the themes that in each meeting are salient for sensitive parenting and sensitive discipline (see Table 1). Themes for sensitive parenting concern the difference between exploration versus attachment behavior, the technique of speaking for the child, and the importance of sensitivity chains and of sharing emotions during parent-child interaction. Themes inherent sensitive discipline concern inductive discipline and distraction, positive reinforcement, sensitive time-outs, and empathy for the child [14, 21]. The first four sessions introduce these relevant topics whereas the two last sessions serve as booster sessions to revise and integrate the themes previously afforded and to reinforce new acquisitions in the parent [21]. The VIPP-SD has been applied to different settings [129–131], including residential facilities [132], and has been successfully adopted with different clinical and at-risk groups [133–135]. Previous meta-analytic work provided evidence for a substantial effect of VIPP-SD in enhancing positive parenting [21]. Treatment will be administered by a group of interveners officially trained and showing fidelity of treatment. Treatment fidelity will be guaranteed through continuous supervisions of the interveners with the fourth author, an official Italian trainer on the method.

**Table 1 Tab1:** Themes relevant for the VIPP-SD

Session	Sensitive parenting	Sensitive discipline
1.	Exploration vs. attachment behavior	Inductive discipline and distraction
2.	Speaking for the child	Positive reinforcement
3.	Sensitivity chain	Sensitive pause
4.	Sharing emotions	Empathy for the child
5.	Booster session	Booster session
6.	Booster session	Booster session

Retrieved from Juffer et al. [21]

#### Wait-list group

The experimental SUD group will be administered the VIPP-SD immediately after the pre-test phase whereas, during this period, participants in the SUD control group will undergo TAU which involves individual and group psychotherapy, psychopharmacological treatment, and educational intervention. After the post-test phase, the intervention will be delivered also to the wait-list group.

### Measures

#### Primary aim

Our primary aim is to investigate whether the intervention is effective in improving the quality of parenting, measured through observed parenting behaviors operationalized as parental sensitivity and sensitive discipline. According to previous work [51], parental sensitivity will be assessed during free play, whereas sensitive discipline will be assessed during two compliance tasks, a do not touch situation and a clean-up situation. Each procedure will be video-recorded and coded by raters blinded to the aims of the study and to the participants’ condition. The observational procedures will be assessed with the Emotional Availability Scales [50], 6 scales that evaluate the parent’s and the child’s contribution to the interaction. Moreover, sensitive discipline will also be assessed through a scale aimed at assessing the presence of verbal or physical harsh discipline [51]. Multiple trained raters, blinded to the study objectives and to the participants’ condition, will code videotapes. Regular meetings with the developers of the coding systems will be scheduled, to guarantee reaching of sufficient reliability with the coding system and avoiding rater drift. Moreover, inter-rater reliability will be calculated on a subset of the videos.

#### Secondary aim

Our secondary aim is to investigate intervention effects on the mothers’ attentional disengagement to infant negative emotions, inhibitory control in front of children’s emotions, and on reflective functioning. A description of the measures adopted for each mechanism is provided in the following sections.

##### Measurement of attentional disengagement 

Maternal disengagement to infant negative emotions will be measured through an attentional bias reaction time paradigm [57]. During this attentional task, subjects are required to focus on a central go/no-go signal on the computer screen (a green or a red cross). A horizontal and a vertical line are presented as peripheral stimuli at the two extremities of the screen. The red central cross represents no-go trials, where participants are required to press the space bar. The green cross indicates go trials, where the individual is required to localize the position of the horizontal bar and press the appropriate keyboard response (A=left, L=right). During the task, distressed or non-distressed infant faces will appear behind the cross, as background images, slowing down the disengagement of attention. Each trial will begin with a fixation cross at the center of the screen (750 ms), followed by the stimulus display (240 ms, including the go/no-go signal, the face stimuli, and the two peripheral lines), and finally a blank screen until a response is registered. Participants are instructed to ignore pictures appearing in the task. An index of attentional bias towards distressed infant faces will be calculated, computing the difference between mean reaction times (ms) on distressed and non-distressed infant trials for each individual [55, 57].

##### Measurement of inhibitory control 

The mothers’ inhibitory control in front of children’s emotions will be assessed on a computerized go/no-go task involving child faces displaying different emotions (positive vs negative). Visual stimuli are selected from the Child Affective Facial Expression set [136], a validated set of 2- to 8-year-old children’s faces. During the emotional go/no-go task, the participants will be randomly presented with a child showing a positive or a negative emotion. Positive emotions represent go trials, where participants are required to press the space bar. Negative emotions indicate no-go trials, where individuals are required to inhibit their behavior, doing nothing. Each trial will begin with a fixation cross at the center of the screen (2000 ms), followed by the stimulus presentation (500 ms), and a blank screen with a fixation point (1500 ms) for response registration. Each of the 60 faces will be shown once, for a total of 60 trials. Reaction times and accuracy of the performance will be recorded and yield a measure of the mothers’ inhibitory control when exposed to children’s affective expressions.

Given previous studies reporting correlations between selective attention and inhibition of action in normative [137] and addicted individuals [63, 138], a preliminary correlational analysis will be carried out on performance on the two cognitive tasks. When the two measures are correlated, a composite score will be calculated [139, 140]. When not, performances at the two tasks will be considered as separate variables in statistical analyses.

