## Background

Quality of parenting plays a fundamental role in infant development [1] and is likely to be severely compromised in the context of maternal substance use disorder (SUD [2];), a clinical condition highly associated with dysfunctional parenting practices that in their most severe forms could lead to child maltreatment [3]. Several authors point to the importance of implementing interventions that besides focusing on the condition of drug abuse or dependence per se also target parental functioning, given that recovery from the first is not necessarily associated to improvements in the latter [4–7]. Moreover, a wide array of studies show the relevance of SUD-related cognitive impairments, as for example deficits in attention, memory, decision-making, and problem solving [8–10], to better understand which mechanisms could mediate the effect of interventions [11, 12]. In this regard, much work has been done with respect to adults with SUD (e.g. [13]), but little is known about how such cognitive impairments relate to parenting and parenting interventions in adults with SUD [7].

The present study protocol describes a randomized wait-list controlled trial in which we aim to examine the efficacy of the Video-feedback Intervention to promote Positive Parenting and Sensitive Discipline (VIPP-SD [14];) in improving the quality of parenting in mothers with SUD. Secondly, the study aims to investigate whether the intervention affects parental cognitive mechanisms, improving attentional disengagement to infant negative emotions, inhibitory control in front of children’s affective expression, and maternal reflective functioning. Finally, the study aims to detect whether changes in parental cognitive mechanisms play a role in mediating the effect of the VIPP-SD program on the quality of parenting measured through observed parenting behaviors. To accomplish this, we will compare mothers with SUD receiving the intervention (SUD experimental group) to mothers with SUD undergoing treatment as usual (SUD control group). Secondly, we will compare mothers with SUD to low-risk mothers recruited from the general population, to see whether the intervention reduces expected differences between mothers with SUD and low-risk mothers. In the following paragraphs, rationale, objectives, hypotheses, and methods of the study are presented, followed by a discussion of the possible implications.

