
### Cognitive mechanisms involved in parenting

#### Attentional mechanisms: attentional bias to child negative emotions

Attentional processing of child stimuli provides one of the basic cognitive mechanisms for sensitive parenting. Human adults present a selective bias in the processing of infant faces, which is of potential evolutionary value [52, 53] since it facilitates a detailed screening of facial mimicry and increases the likelihood of appropriate responses [54]. It has been shown that mothers present a preferential attentional bias for child negative emotions, finding it more difficult to disengage their attention from visual stimuli displaying sadness or distress [55, 56]. This process is attenuated in the presence of psychopathology and high parenting stress [53, 57] and has proved to be sensitive to treatment [54]. We hypothesize this same attentional mechanism to be disrupted in mothers with SUD, given the high incidence of parenting stress [58], psychopathology [59, 60], and the overlap between brain reward regions associated to substances and to infant-related stimuli [61, 62]. This hypothesis is further supported by studies that provide evidence for disruptions in normative attentional processes in the context of substance dependence [63, 64].

In the current study, we aim to test whether attentional bias to child face in mothers with SUD, measured with a computerized neuropsychological task, is enhanced through the application of the VIPP-SD. According to previous studies, we expect that (1) attentional bias to child negative emotions in mothers with SUD increases after the intervention compared to the randomized control group receiving TAU and (2) at pre-test, mothers with SUD will show lower attentional bias to child negative emotions compared to the low-risk group.

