### Aims and hypotheses

Our primary aim is to investigate intervention effects on the quality of parenting measured through observed parenting behaviors, in mothers with SUD. We will investigate whether the intervention affects sensitive parenting and gentle but consistent discipline. We expect that, from pre-test to post-test, the quality of observed parenting in the SUD experimental group increases more or decreases less than in the SUD control group.Our secondary aim is to investigate intervention effects on parental cognitive mechanisms. We will investigate whether the intervention affects the mothers’ performances on (2a) an attentional bias reaction time paradigm aimed at measuring attentional bias to negative emotions and on (2b) a go/no-go task involving child faces displaying different emotions aimed at measuring inhibitory control in response to child emotions, respectively. Moreover, we will investigate whether the intervention affects (2c) self-perceived reflective functioning. We expect that the intervention modifies the mothers’ performances on the two tasks and self-reported reflective functioning in the SUD experimental group with respect to the SUD control group.Our tertiary aim is to investigate whether changes in parental cognitive mechanisms affect intervention effect on parenting. Specifically, we will investigate whether changes in the mothers’ (3a) attentional bias, (3b) inhibitory control, and (3c) reflective functioning account for changes observed in parenting. Specifically, we expect that improvements in the mothers’ performances on the cognitive measures will be associated to improvements in the quality of observed parenting in the SUD experimental group (Fig. 1).Our fourth objective is to explore whether the administration of the intervention has an effect on parenting stress. Specifically, we expect that, after the administration of the VIPP-SD, perceived parenting stress in the SUD experimental group decreases compared to the SUD control group.Our fifth objective is to compare the SUD experimental group and the SUD control group to the low-risk group with respect to post-test measures.

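### The rule that merges the attention and go/no-go measures when they correlate conflicts with aims 2a/2b and 3a/3b, which ask about each mechanism separately

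*Protocol article*

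**What the plan says.** Aims and hypotheses lists the two tasks as distinct secondary questions: "2a) an attentional bias reaction time paradigm aimed at measuring attentional bias to negative emotions and on (2b) a go/no-go task". The mediation aim keeps them distinct, asking whether changes in "3a) attentional bias, (3b) inhibitory control, and (3c) reflective functioning account for changes observed in parenting". The Tertiary aim section under Measures again names both tasks. General executive functioning goes further: it plans an adjustment meant to isolate the programme's effect on inhibition in response to child emotions.

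Measurement of inhibitory control adds a data-dependent step: "a preliminary correlational analysis will be carried out on performance on the two cognitive tasks". Two branches follow. The first is "When the two measures are correlated, a composite score will be calculated"; the second is "When not, performances at the two tasks will be considered as separate variables in statistical analyses". The article states no threshold, time point, group of mothers, sign condition or formula for the composite. Statistical analyses does not return to the matter.

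On direction, the attention index is obtained by "computing the difference between mean reaction times (ms) on distressed and non-distressed infant trials", so a larger value means slower responses when the face is distressed. The hypothesis is that "attentional bias to child negative emotions in mothers with SUD increases after the intervention". The Background describes the aim as "improving attentional disengagement to infant negative emotions".

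**The concern.** The aims and the measurement rule cannot both be followed in every case. If the tasks are judged correlated, one score takes the place of two, and aims 2a, 2b, 3a and 3b lose the variables they are stated in. A composite that changes could reflect either task or both. One that mediates could not be attributed to attention or to inhibition, which is the question the trial sets itself.

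Whether this happens depends on an observed correlation in a small sample, judged by an unstated criterion. A composite also dilutes an effect confined to one task. Finally, the wording on attention leaves the favourable direction of one component unclear, and that direction must be settled before any averaging.

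**Working it through.** The protocol gives no figure for this rule, so there is none to reproduce. Its planning effect, d = 0.47 (Sample size and power, applied there to the secondary aims as well), serves as the benchmark.

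**1. How often the composite would be triggered**

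Inputs: 40 mothers with SUD (Recruitment). Assumptions: correlated means two-sided p < 0.05, and the true correlation r ranges from 0 to 0.5.

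- Cut-off: r_c = t/√(n − 2 + t²). With n = 40 and t = 2.024, r_c = 2.024/√(38 + 4.098) = 0.312.
- Probability of merging, with z = atanh: 1 − Φ[(z_c − z_r)√(n − 3)] + Φ[(−z_c − z_r)√(n − 3)].
- Example at r = 0.3: z_c = 0.3228, z_r = 0.3095, √37 = 6.083. The first part is 1 − Φ(0.081) = 0.468 and the lower tail is negligible.

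| True r | 0 | 0.2 | 0.3 | 0.4 | 0.5 |
|---|---|---|---|---|---|
| P(merge), n = 40 | 0.05 | 0.23 | 0.47 | 0.73 | 0.92 |

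The analysis set matters too. The low-risk mothers take the same tasks, so 60 could be used; the stated minimum sample is 34. The cut-off is 0.339 at n = 34 and 0.254 at n = 60. At r = 0.3 the merging probability is then 0.41 or 0.65, against 0.47 at n = 40.

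**2. What merging does to the effect**

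Assume two unit-variance scores with correlation r, equally weighted. The standardised composite effect is (d1 + d2)/√(2 + 2r). At r = 0.3 the denominator is √2.6 = 1.612.

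- One task responds (0.47 and 0): 0.47/1.612 = 0.29, a loss of 38%. Over r = 0.2 to 0.5 the effect is 0.30 to 0.27. Aligning signs does not prevent this.
- Both respond in the hypothesised direction, signs aligned (0.47 and 0.47): 0.94/1.612 = 0.58. Over r = 0.2 to 0.5 it is 0.61 to 0.54.
- Both respond but enter with opposite signs (0.47 and −0.47): 0.

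These are effect sizes, not power, because power also depends on the correlation between repeated measures, which the protocol does not state.

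**3. Type I error**

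The two-branch rule was simulated under no treatment effect (n = 40, 4,000 runs, correlation tested at baseline with both arms pooled).

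| True r | Any significant result, rule | Any significant result, always two tests |
|---|---|---|
| 0 | 0.100 | 0.104 |
| 0.3 | 0.078 | 0.100 |
| 0.5 | 0.058 | 0.095 |

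In the runs where the composite was chosen, its own error rate was 0.035 to 0.057. The r = 0 value (0.035) rests on only about 200 merged runs.

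**4. Direction**

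The index and the hypothesis agree: a larger reaction-time difference is more bias, and an increase is expected. The Background phrase about improving disengagement reads the other way, since a larger index means slower disengagement. Inhibitory control is also expected to increase, but it is to be derived from reaction times and accuracy, with no single score or sign fixed.

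**The case against.** The rule is stated in advance, has two defined branches, and looks at the association between tasks rather than at the treatment contrast. It cites earlier work for expecting a correlation. Under the protocol's own hypotheses both constructs increase, and a sign-aligned composite then carries a larger effect than either task alone. Threshold, time point and weighting are details that an article commonly leaves to the analysis plan. All of this stands, and the missing details alone would not make a finding. What it does not answer is the conflict: however the trigger is defined, the composite branch removes the variables that the aims are written in.

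A reader might infer three stronger points, which the documents do not support:

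- **That the choice is a coin toss.** This is true only near r = 0.3 under the assumed p < 0.05 rule at n = 40. The protocol gives none of these values except the 40 mothers.
- **That the two components point in opposite directions, so a real effect would cancel.** Both are hypothesised to increase. Opposition would need inhibition scored so that lower is better, for example as an error count, and then an unaligned sum. Neither is planned.
- **That the rule inflates false positives.** It does not if the correlation is tested on pooled baseline data. A correlation taken at post-test across both arms could itself reflect treatment, but the protocol does not say that post-test data will be used.

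**Conclusion.** The concern holds as a conflict between the measurement rule and aims 2a/2b and 3a/3b. If the composite replaces the two measures, the separate mechanism questions go unanswered. The chance of this cannot be fixed from the protocol: it runs from 0.05 to 0.92 for true correlations of 0 to 0.5, assuming two-sided p < 0.05 and n = 40. The effect on the result can go either way: from 0.47 down to 0.29 if one task responds, or up to about 0.58 if both respond with signs aligned (r = 0.3, equal weights, unit variances). Cancellation is a possibility left open, not something planned. The wording on disengagement is a smaller inconsistency to be settled alongside. The point merits correction, but it touches secondary and tertiary aims only; the primary outcome is unaffected.

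**What to change.** - Delete the correlation-triggered replacement. Always analyse the attention index and the go/no-go measure separately for 2a/2b and for 3a/3b.
- If a composite is wanted, define it now as supplementary: the average of sign-aligned z-scores, standardised on pooled pre-test data.
- Reconcile the Background wording on improving disengagement with the hypothesis that attentional bias increases, so that one expected direction is stated for the index.

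The cost is a change of wording in the analysis plan. There are two tests instead of one when the tasks correlate, and the composite's gain when both tasks respond moves out of the main secondary analysis into a supplementary one.

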##### Measurement of maternal reflective functioning

Maternal reflective functioning will be assessed using the Parental Reflective Functioning Questionnaire [141], an 18-item self-report measure aimed at investing perceived reflective functioning in parents, intended as curiosity about the child’s mental states, effort/refusal to understand mental states, and how they relate to behavior.

#### Tertiary aim

Our tertiary aim is to investigate whether changes in the mothers’ emotional modulation of inhibitory control, attentional disengagement, and reflective functioning account for changes in the quality of parenting. To do this, we will examine whether changes in the mothers’ performances on the attentional bias reaction time paradigm and on the go/no-go task involving child faces displaying different emotions, as well as maternal self-reported reflective functioning, account for changes in observed parenting behaviors.

#### Fourth aim

Our fourth objective is to explore whether the administration of the intervention has an effect on parenting stress, which will be measured through the Parenting Stress Index – Short Form [92], a 36-item self-report measure aimed at investigating the stress experienced by parents during parental practices.

#### Fifth aim

Our fifth objective is to compare the SUD experimental group and the SUD control group to the low-risk group. To do this, we will compare the post-test measurements of the experimental and control SUD groups with the two assessments in the low-risk comparison group.

